**Fig. 1 Fig1:**
[figure not shown]
Participant flowchart

Recruitment procedures will vary slightly across the two sites. Adults will be recruited who are on the waiting list and are not yet receiving ADHD medication. In the UK/British Isles, the clinical team will contact the individuals by their preferred method of contact (post, email, or telephone) and will provide them with information about the study. If the patient is interested in taking part, the first baseline assessment with the research team will be scheduled. The participant information sheet and informed consent form will be sent to patients a minimum of 24 h before the baseline assessment. In Spain, individuals will be provided with information about the study on the day of their ADHD assessment. If the patient is interested in taking part, the baseline assessments will be completed on the same day. Written informed consent will be obtained.

The baseline assessments will happen either in-person or virtually using Microsoft Teams depending on the site they have been recruited from. In the UK/British Isles, participants will be paid £30 at the point of enrolling in the study, and a further £5 for every completed outcome measure (paid at months 6 and 12). Participants will be paid an additional £30 at the end of the study period (month 12). In Spain, participants will not receive any financial compensation for their participation.

The baseline assessments will take approximately four hours to complete. In Spain, the two in-person baseline assessment sessions will be completed in one day. In the UK/British Isles, the virtual baseline assessment sessions will be completed across two days, with approximately a week in between each session. Both the in-person and virtual baseline sessions will consist of (1) the Diagnostic Interview for ADHD in Adults (DIVA [40]) to confirm an ADHD diagnosis, (2) a brief IQ and short-term working memory test [41, 42], (3) Mini International Neuropsychiatric Interview (MINI [43]) to establish psychiatric comorbidities, (4) two baseline questionnaires: a demographic About You questionnaire and the Autism Spectrum Quotient questionnaire (AQ-10 [44]), (5) two cognitive tasks of the Combined cued continuous performance test and Go/NoGo (CPT/GNG) task and the Fast task (while researcher present), (6) completion of questionnaires and physical measurements of weight, waist circumference and blood pressure, (7) training session on the smartphone, wearable device and blood pressure machine, and (8) guidance on how to collect DNA saliva sample and microbiota sample (optional). Participants will be able to take breaks during the session if required.

During the baseline session, the participants with ADHD will also be asked to identify a partner, a family member or a close friend who could complete informant-report versions of the active monitoring questionnaires on ADHD symptoms and impairment, and irritability, using the Research Electronic Data Capture (REDCap), a web-based platform. The research team will contact the partner, family member or close friend (via email or telephone) and invite him/her to complete the questionnaires every four weeks.

### Remote data collection

The﻿ r﻿emote monitoring starts immediately following the research baseline assessment and will last for 12 months. The remote monitoring consists of both active and passive components, following procedures established for the wider ART research programme, and is linked to the RADAR-base mobile-health platform [32]. Below is a summary of the methods of remote data collection used in the ART-CARMA study (Fig. 2).

**Fig. 2 Fig2:**
[figure not shown]
ART-CARMA active and passive monitoring

#### Active App

Participants will be asked to download the RADAR-base Active App that requests the participant to complete questionnaires at specific intervals. Every day participants will be asked to complete a short questionnaire for medication use on whether the participant took their medication that day, with follow-on questions on type and dose of medication or why medication was not taken (e.g., experienced side effects, forgot to take their medication, or chose not to take their ADHD medication that day). Every week participants will be asked to report their medication use side effects using the CADDRA Patient ADHD Medication form [45]. This form contains four items on changes experienced since starting medication and 28 items on side effects. Every four weeks, participants will be asked to complete a longer set of questionnaires: ADHD symptoms and impairments will be measured using the Barkley Adult ADHD Rating scale on current symptoms (BAARS-IV) [46] and Barkley ADHD functional impairment scale [46]. This includes the 18 diagnostic ADHD symptoms and 10 items on functional impairment; Depression will be measured using the 8-item Personal Health Questionnaire Depression Scale; PHQ-8 [47], which is a widely used measure of current depression in the general population; Anxiety will be measured using the 7-item Generalized Anxiety Disorder questionnaire; GAD-7 [48], which provides a dimensional score of anxiety symptoms; Aggression will be measured using the 23-item Reactive-Proactive Aggression Questionnaire for Adults; RPQ-A [49]; Irritability will be measured using the self-reported 7-item Affective Reactivity Index questionnaire; ARI-s [50]; Smoking behaviours will be measured the 6-item Test Fagerstrom questionnaire [51]; Alcohol use will be measured using the Alcohol Use Disorders Identification Test; AUDIT [52]; Diet will be measured using the 14-item Mediterranean diet adherence questionnaire [53]; Blood pressure and weight measurements will also be taken. Participants will be provided with an Omron M2 Basic blood pressure monitoring machine, weighing scales and a tape measure; Major life events will be measured every 6 months using the 13-item List of Threatening Experiences; LTE [54]. The participant will also be asked to complete a short speech task monthly, on the Active App.

Participants will also self-administer the two cognitive tasks of CPT/GNG and Fast task twice during the 12 months (months 6 and 12) on their home PC or laptop, without the researcher present. In addition, ratings on ADHD symptoms are obtained monthly also from a partner, a family member or a close friend of the individual with ADHD using web-based Redcap.

#### Passive App

Participants will be asked to download the RADAR-base passive remote monitoring app, configured for ART requirements [32], which will run in the background, requiring no further input from participants. The Passive App collects data on ambient noise, ambient light, phone usage information (e.g., which apps were used and how long, when the phone was unlocked), passive audio, Global Positioning System (GPS) location, Bluetooth connectivity, battery life, gyroscope, steps and acceleration. Features of the passive audio, rather than raw audio itself, are extracted from the audio on the phone for transmission. GPS location data will be randomised; that is, providing relative location data, not absolute coordinates. This prevents identification of an individual’s home address or precise geographical location.

#### Wearable sensors

The wearable device in ART-CARMA is the Empatica EmbracePlus [34]. Participants will be asked to wear the device for the duration of the study (12 months), which will provide ongoing data collection of PR, PRV, systolic peaks, electrodermal activity, oxygen saturation (SpO2), peripheral temperature, and acceleration. By combining data across these variables measured, processes such as physical activity, sleep, autonomic arousal, and indicators of cardiovascular health can be captured.

#### Empatica Care App

The Care App collects data from the EmbracePlus and sends it to the Empatica Cloud, where it is stored. The data collected by the EmbracePlus is transferred to the Care App via Bluetooth®. The Care App then transmits the data to the Empatica Cloud via WiFi. To access and use the Care App, the participant has to scan the QR code or type in the participant ID/password provided by the research team. The login credentials generated by the research team via the Care Portal are unique and de-identified.

#### Compatible Android smartphone

Both the Passive App and the EmbracePlus require compatible smartphones to be used in ART-CARMA. The Passive App requires an Android smartphone and the EmbracePlus requires Bluetooth® 5.0. For participants who do not own a smartphone, we will provide a compatible Android smartphone for them. For participants who are using a non-Android or a non-compatible Android smartphone, we will not recruit them unless they agree to switch to a compatible Android smartphone as their only phone for the duration of the study. We will provide a compatible Android smartphone for them.

### Outcome measures

The outcome measures are (i) the cardiometabolic risk factors (HR, blood pressure, weight, smoking, alcohol use, diet, sleep, physiological stress response) and (ii) daily medication use (adherence), adverse side effects and other reasons for non-adherence.

#### Process evaluation

To ensure a system which meets participants and researcher needs, there will be continued monitoring of the ART system throughout the data collection period, including participant adherence to wearable devices and smartphone, and completion of measures. At the study endpoint, we will offer post-participation qualitative interviews to participants. Interviews will be offered to all participants who completed to the study end-point and to those who dropped out during their 12-month study period.

#### Follow-up procedure and data monitoring

Participants will be contacted by telephone after one month of the baseline assessment to address any concerns or questions. Brief follow-up phone-calls will then be offered every three months to maintain engagement with participants throughout the course of the study and to remind participants of any upcoming assessments. Participants will be encouraged to live their lives as normal, responding to the Active App notifications when required. The research team will be able to review incoming data using the RADAR-base management portal and Empatica Research Portal. The research team may contact participants if there is a loss of data from a device. All contact with participants will be recorded as evidence of feasibility and acceptability of outcomes.

### Study debrief

At the end of the follow-up period, participants will receive a ‘debrief’ session, which will serve to collect end-point acceptability and usability outcomes, and to retrieve study materials (devices, chargers etc.). This will be done either over the phone or on Microsoft Teams with a member of the research team and will be audio-recorded using Microsoft Teams. Participants will also have an opportunity to view and discuss their own data.

### Adverse events and study withdrawal

There may be several reasons for withdrawal from the study:

Participant choosing to no longer participate: participants will be informed both in writing and verbally that participation is voluntary, that non-participation will not influence their medical care, and that they are free to withdraw from the study at any point without providing reasons.The research team may withdraw the participant in the event of inter-current illness, adverse event (AE), protocol violation, administrative or other reasons.

In the case of participant self-withdrawal, all attempts will be made to follow up with the participant to establish cause of withdrawal, and to collect qualitative data regarding experience of participation. All data, including those from withdrawn participants, will be included in the final analysis. If a participant withdraws from the study prematurely, we will consider replacing the participant if resources allow and if recruitment is ongoing for the study.

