ART-CARMA has six specific objectives:Objective 1: Use RMT to identify real-world consequences of ADHD medication treatment on the following cardiometabolic risk (or protective) factors in adults with ADHD: changes in HR, blood pressure, weight, smoking, alcohol use, diet, sleep and physiological stress response.Objective 2: Use RMT to measure the potential contribution of physical activity to a reduction in these risk factors, independently and in combination with ADHD medication treatment.Objective 3: Use machine learning, applied to the full set of multimodal remote monitoring data from the 12-month period, to build prediction models of the cascade of effects that follow from the initiation of ADHD medication treatment. This allows us to go beyond objectives 1 and 2, to obtain insight into potential underlying mechanisms that are needed for developing algorithms for personalised treatment. The prediction models allow us to assess complex, temporal relationships between multiple measures.Objective 4: Use RMT to explore ADHD medication use patterns in adults with ADHD in the first year of starting ADHD medication treatment (including treatment initiation, titration and the subsequent period) and to quantify the extent of treatment adherence, non-adherence and treatment gaps.Objective 5: Use RMT to identify potential reasons for non-adherence, with a focus on adverse side effects (e.g. daytime sleepiness and changes in electrodermal activity indexed arousal/alertness, changes in heart rate or blood pressure, changes in appetite/weight, increased anxiety/depressive symptoms or irritability, not feeling themselves/feeling their personality changes when on medication, tics, dizziness, sweating, headaches), lack of treatment response (limited or no effect on ADHD symptoms and impairments) and poor adherence behaviours (e.g. forgetting to take or difficulties taking ADHD medication). We capture these time series data across the periods of pre-treatment, treatment initiation, titration and subsequent monitoring.Objective 6: Identify psychiatric comorbidities that predict treatment non-adherence or increase adverse effects. We will measure symptoms of autism spectrum disorder, antisocial behaviour, anxiety, depression and substance use.

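### No described contact with participants who leave asks about ADHD medication status, so use after exit or after the app falls silent is unobserved and plausibly informatively censored

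*Protocol article*

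**What the plan says.** All references are to the protocol article.

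- **What is to be estimated.** Under Study objectives, Objective 4 covers the first year of treatment and sets out "to quantify the extent of treatment adherence, non-adherence and treatment gaps". Objective 5 asks why people do not adhere. Outcome measures names daily medication use as an outcome.
- **How it is measured.** Under Active App: "Every day participants will be asked to complete a short questionnaire for medication use on whether the participant took their medication that day". Follow-on items record type and dose, or the reason for a missed day. A side-effect form is completed weekly. No second source, such as clinic or prescription records, is described.
- **What happens on withdrawal.** Under Adverse events and study withdrawal, where someone chooses to leave, the plan is this: "all attempts will be made to follow up with the participant to establish cause of withdrawal, and to collect qualitative data regarding experience of participation". The team can also end participation: "The research team may withdraw the participant in the event of inter-current illness, adverse event (AE), protocol violation, administrative or other reasons". No follow-up contact is described for that second group. The section adds: "All data, including those from withdrawn participants, will be included in the final analysis". On replacement: "we will consider replacing the participant if resources allow and if recruitment is ongoing for the study".
- **Other contacts.** Under Follow-up procedure and data monitoring, a month-1 call deals with participants' worries and queries. After that, "Brief follow-up phone-calls will then be offered every three months to maintain engagement with participants", and these calls also serve as reminders of assessments. The team may get in touch when device data stop arriving. Process evaluation offers qualitative interviews, including to those who dropped out. Study debrief covers acceptability, usability and return of equipment.

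**The concern.** The contact with leavers has a stated purpose, and the study's own outcome is not part of it. Once someone leaves or stops answering the app, nothing described says whether that person is still taking medication or when they last did.

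This matters because the loss is unlikely to be unrelated to adherence. The article lists forgetting, side effects and choosing not to take the medication among the reasons for non-adherence. Forgetfulness could also end app completion, and side effects could prompt someone to leave the study. An adverse event is itself a listed ground for the team to withdraw a participant, and that is the group for whom no contact is described. At stake are the extent of non-adherence and gaps under Objective 4, and the reasons for stopping under Objective 5.

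The timing also matters. How missing adherence data are modelled can properly be left to an analysis plan. A status and a stop date that were never asked for cannot be supplied by one.

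**Working it through.** **1. Match each contact to the outcome.**

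- Daily app item: records medication use and reasons, but ends when the participant leaves or stops responding.
- Exit contact (self-withdrawal): cause of leaving and experience of taking part. Medication status not listed.
- Withdrawal by the team: no contact described.
- Month-1 and three-monthly calls: queries, engagement, reminders. Medication status not listed.
- Contact about lost device data: concerns data flow. Medication status not listed.
- Drop-out interview and debrief: qualitative experience, acceptability, usability. Medication status not listed.

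So a stop reported before exit is dated and carries a reason. Use after exit, or after app silence, is not recorded by any described step. Replacing a leaver adds a new person but does not recover the leaver's status.

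**2. Is there a figure in the plan to reproduce?** No. The article states no dropout rate and no expected adherence or persistence. Its sample-size section sets 280 for the power calculation against 300 to be recruited, a margin of 20/300 = 6.7%, but does not call this a dropout allowance.

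**3. Illustration, with assumed inputs.** Take a simple summary: the share still on medication at the end of monitoring. The article does not specify this estimator; it is used only to show scale. Let

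- p = share on medication among those whose status is known (assumed 0.60),
- u = share of the cohort whose status is unknown (assumed 0.20 or 0.30),
- q = share on medication among those of unknown status.

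Whole-cohort value = (1 − u)p + uq. With q anywhere from 0 to 1, the bounds are (1 − u)p and (1 − u)p + u:

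- u = 0.20: 0.80 × 0.60 = 0.48, and 0.48 + 0.20 = 0.68, so 48% to 68%.
- u = 0.30: 0.70 × 0.60 = 0.42, and 0.42 + 0.30 = 0.72, so 42% to 72%.
- u = 20/300, the margin in step 2: (280/300) × 0.60 = 0.56, and 0.56 + 0.067 = 0.627, so about 56% to 63%.

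The width of the interval equals u, whatever p is.

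**4. Direction.** Reporting p for the whole cohort errs by p − [(1 − u)p + uq] = u(p − q). With q = 0.30, half of p:

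- u = 0.20: 0.20 × 0.30 = 0.06. The true value is 54%, overstated by 6 points.
- u = 0.30: 0.30 × 0.30 = 0.09. The true value is 51%, overstated by 9 points.

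The error is zero if q = p and changes sign if q exceeds p. With a different assumed p of 0.70 and q = 0.20, it is 0.20 × 0.50 = 10 points at u = 0.20 and 0.40 × 0.50 = 20 points at u = 0.40.

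**The case against.** The strongest reply is that much of the record survives. The daily log dates and explains any stop reported before exit, and the article says withdrawn participants' data are analysed. A reader might infer that all information on whether and when leavers stopped is lost, or that adherence is estimated only among those who stay. The documents support neither. Leavers contribute up to the point they leave, and the planned mixture latent Markov models are not restricted to completers. What remains is censoring that is plausibly informative.

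A second reply is that the cause of withdrawal, or a drop-out interview, may reveal that medication was stopped. That stands in part: it may, but not as a dated item asked of everyone.

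Third, the article condenses a fuller protocol, and call scripts usually sit elsewhere. This limits how firmly the gap can be stated. However, the article does state what each contact is for, and medication status is absent from all of them.

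Fourth, the illustration uses invented inputs and an estimator that the article does not name. This is correct. The bounds lie on both sides of the assumed 60%, so the direction of bias is a reasonable expectation, not a result.

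A reader might also see a contradiction between telling participants that "they are free to withdraw from the study at any point without providing reasons" and then trying to learn the cause. There is none: the team may ask and the participant may decline.

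**Conclusion.** The point holds as a gap in data collection. Within the procedures described, ADHD medication use after exit or after app silence is unobserved, for self-withdrawal and for withdrawal by the research team alike. Because leaving and stopping plausibly share causes, the censoring may bias the Objective 4 estimates and the Objective 5 reasons, probably toward better adherence.

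The size cannot be derived from the article. Under the assumed 60%, a 20% unknown share leaves a range of 48% to 68%. A 6-point overstatement follows only if those of unknown status persist half as well as the rest, and there is none if they persist equally. These figures show scale and do not estimate the study's bias. The change is a cheap improvement worth making while data are still being collected, because no later analysis can restore answers that were not sought.

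**What to change.** Keep the planned follow-up attempts and add a short set of optional scripted items:

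- currently taking ADHD medication, yes or no;
- date of last use;
- if stopped, whether the participant or the prescriber ended it.

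Ask these at the exit contact, and extend that contact to participants withdrawn by the research team. Ask the same items in the month-1 and three-monthly calls, so that someone who later stops answering the app has a last known status. Add a line to the information sheet saying that these questions may be asked and need not be answered.

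The cost is a few questions in contacts mostly already planned, one further contact for team-initiated withdrawals, and the information-sheet line. Calls become slightly longer, and some leavers will decline, so the gap narrows but does not close. The change concerns data collection only and leaves usual care untouched.

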### Statistical and analysis plan

Descriptive statistics for demographics, attrition rate and number of participants using the remote assessment measurements without loss or damage and providing adequate data for the duration of the study period will be estimated. Using a survival model approach [55] and clustering analyses, we will investigate whether any demographics and/or other numerical information obtained during baseline of the study might serve as a predictor for subject drop out/percentage of adequate data. Using mixed-effect models with participants as a random factor, we will estimate whether relationships between the amount of usable data during the weeks prior to the outcome assessment and obtained scale’s measurements exist.

Regression and machine learning approaches will be used to investigate the changes in cardiometabolic factors measured by RMT (listed in Objective 1) following initiation of ADHD treatment. Data obtained from the accelerometer will be used to label days/part of the days with different gradation levels of activity levels and the duration of such activities on a per day basis. For Objective 2, Activity and derived features will be used to statistically test the effect of average activity level on cardiometabolic factors defined in Objective 1 with/without treatment. As well as typical statistical modelling approaches, this analysis will utilise both conventional machine learning methods including support vector machines and random forest in combination with feature selection and fusion approaches, as well as more contemporary deep learning methods (Objective 3).

Actigraphy read-outs will also be used to derive sleep characteristics using Empatica’s proprietary, 2-step algorithm that automatically identifies sleep periods and within the determined sleep period classifies epochs as sleep or wake with a 1-minute granularity. Sleep data will be further analysed in relation to Active App data and outcome scales. Utilizing EmbracePlus’ sensor suite, sleep analyses can further be refined by looking at sleep and wake timing, wake bouts, sleep efficiency and fragmentation, activity level(s) over the day during wake (based on 3-axis accelerometers), several features of EDA during wake (gated with motion and temperature) and sleep (including sleep storm patterns). Empatica’s team is also able to post-process EmbracePlus’ sleep or rest data to obtain estimates of respiration and PR, controlling for several factors (movement artefact and compliance) in its processing [56–59]. Raw, regularly sampled blood volume pulse (BVP) data will be used to estimate PR and PRV metrics and respiratory dynamics that result from the interplay of the sympathetic and parasympathetic nervous system. The extraction of features from the homogeneous sample of remotely monitored biosignals will be done according to well-established and openly documented methods (e.g., Task Force of the European Society of Cardiology and the North American Society of Pacing and Electrophysiology). Artefacts will be detected, and the signal noise will be appropriately filtered when it is possible. Spectral and time-domain features extracted from continuous biosensor data will be aggregated across a period of time using statistical characteristics, aligned and collated with features extracted from smartphones, assessments and Redcap, for statistical analysis.

Medication use clustering will be analysed for details around behaviour and pattern of use in Objective 4 and extended in Objective 5 to look at specific predictors of use. Time-variant clustering will be used to define subgroups of medication use classes across time, including the probability of transitioning between classes using mixture latent Markov models.

Machine learning will be implemented in order to build individualised prediction models for treatment response, symptom classification and stratification, and medication adherence (Objective 6). Based on previous work, different prediction models including Neural Processes model personalization and meta-learning techniques, developed for few-shot learning to individualize models, will be used [60].

